**Figure 1 F1:**
[figure not shown]
Study design flow chart.

**Figure 2 F2:**
[figure not shown]
Timeline of the study along with physical and biomarkers assessments.

### Sample Size Calculation

The sample size was calculated with reference to the study by Amini et al. who showed BP differences between neonates from normotensive and pre-eclamptic mothers (28). The difference in systolic BP (SBP) was very high in pre-eclamptic mothers (68.2 ± 1.49 mmHg) compared to normotensive mothers (49.85 ± 5.49 mmHg). Because of the very high SBP variance and standard deviation in the pre-eclamptic group, we decided to use the diastolic blood pressure (DBP) values (normotensive: 30.17 ± 11.89 mmHg vs. pre-eclamptic: 42.11 ± 11.49 mmHg) for the sample size calculation. The software-R, version 4.1.0 (R Core Team, St. Louis, Missouri, USA) was used for the sample size calculation with parameters: alpha = 0.01, mean difference = 11.94 and standard deviation = 0.05. The calculated total sample size is 98 (49 cases and 49 controls). We assumed that not all participants would return for the follow-up and therefore adjusted our sample size by 20% to compensate for possible loses to follow-up. Thus, the total sample will be 98/(100–20/100) = 122 neonates. This implies that the study will commence with the recruitment of 122 pregnant women (61 pre-eclamptic women and 61 normotensive pregnant women) who meet the selection criteria.

### Data Collection

A standard interviewer administered structured questionnaire will be used to collect information on maternal health and cardiovascular risk factors at the beginning of the study (Supplementary file 1–Cardiovascular risk questionnaire). This information will include socio-demographics (sex, age, ethnicity, and location), socio-economic status (marital status, profession, income/revenue, and living standard), maternal obstetric history, family history, cardiometabolic health history, and cardiovascular risk factors (physical exercise, smoking, alcohol consumption, and feeding habit).

### Physical Assessments

Anthropometric measurements will be done in accordance with the international standards guidelines (29). A wall-mounted Harpenden stadiometer will be used to measure participants height to the nearest 0.1 cm while weight will be measured using a wireless weight scale (Tanita body composition scale). In pregnant women, BP including the SBP, DBP, and heart rate will be measured after a 10 min of rest in the seated position using the Omron M HEM-907XL Professional Blood Pressure Monitor (Omron Healthcare, Kyoto, Japan) described by Muntner et al. (30) in triplicates at 3 min intervals. The oscillometric technique (Dinamap 8100) will be used for BP measurement according to the standard protocol for assessment of BP measurement in newborns by Nwankwo et al. (31). An ultrasound device will be used to assess the morphometry, architecture and vasculature of the placenta. This will include assessing the uterine, umbilical and middle cerebral arteries and uterine artery mean pulsating index determined. Foetal cerebroplacental ratio and anthropometry will be calculated when possible.

### Assessment of Arterial Stiffness and Ankle-Branchial Index

A vicorder device (SMT Medical GmbH&Co., Wuerzburg, Germany) will be used for the assessment of pulse wave velocity (PWV), a measure for arterial stiffness and ankle-brachial index (ABI). Brachio-femoral PWV will be done as reported by Alwan et al. (32). Prior to PWV measurements, participants will be asked to lie in a supine position and rest for 10 min. Thereafter, a standard 10 cm pressure cuff will be placed on the upper right thigh as high as possible toward the crotch while another thin pressure cuff will be placed around the neck just on the carotid artery. The distance between the neck and thigh cuffs will be measured in cm using a measuring tape. Pressure lines: red pressure line to the neck cuff and blue pressure line to the thigh cuff, will be connected to the vicorder. Participants details including the BP, weight, height, and length between the carotid and femoral arteries will then be entered into the vicorder software and the test will be conducted. The PWV (m/s) will be calculated as a ratio of path length (between carotid and femoral arteries) and transit time. Prior to the measurement of ABI, a pressure cuff will be placed around the right arm of the participant and another pressure cuff around the ankle of the same side of the body. Participants details (BP, weight, and height) will be entered into the vicorder software while fixing the target SBP of 200 mmHg and the test conducted. The ABI will be calculated as the ratio of the SBP of the ankle and branchial regions.

### Microvascular Assessment by Retinal Imaging

The retinal microvasculature will be assessed for vascular changes via retinal imaging as previously reported (33). A digital retinal camera (Optomed, [name], Finland) will be used to capture the eye fundus for retinal vessel imaging. After capture of the right and left eye fundus, a trained grader, masked to participant's characteristics will perform vessel measurements on the optic disc–centred image. After measurements, a semi-automated IFLEXIS software (VITO, Belgium) will be used to analyse different retinal features including the microvascular state, the retinal vessel dimensions, and vascular tree (34, 35). This will be achieved by calculating the vessels widths and pattern features including the fractal analysis, lacunarity, and tortuosity. The average diameter of arterioles and venules of the eye will be summarised as central arteriolar equivalent (CRAE) and central retinal venular equivalent (CRVE), respectively (36).

### Biomarker Assessments

Blood and cord blood sample will be collected from pregnant women and early morning mid-stream urine samples will be collected from their offspring by the research nurse. These samples will be used to measure oxidative stress markers [lipid peroxidation, total antioxidant capacity, and 8-hydoxyl-2-deoxyguanine (8-OHdG)], lipid profile markers (total cholesterol, triglycerides, LDL-cholesterol, and HDL-cholesterol), insulin resistance markers [fasting glucose, insuli, and glycated haemoglobin (HbA1c)], endothelial function markers [endocan, nitric oxide (NO), and asymmetric dimethyl arginine (ADMA)] and renal function markers [glomerular filtration rate (GFR), creatinine and albumin] (37, 38). Fasting glucose and insulin will be used to calculate the homeostatic model assessment of insulin resistance (HOMA-IR) while urinary albumin and creatinine will be used to calculate the albumin to creatinine ratio (ACR) (37, 38).

### Statistical Analysis

STATA (Stata, College Station, Texas, USA) and IBM statistical package for social sciences (SPSS) Version 23.0 (IBM Corp). Armonk, NY, USA) will be used for data analyses. The Shapiro-Wilks test will be used to check for normality and data will be log-transformed and/or corrected for outliers when necessary. Descriptive statistics will be employed for data presentation as mean ± standard deviation (SD) or median ± interquartile range (IQR) for continuous variables and proportions (percentages) for categorical variables. Independent sample *t*-test will be used to compare mean differences between groups (pre-eclamptic and normotensive pregnant women and their offspring). Multivariate analysis using multiple analysis of variance (MANOVA) will be used to compare continuous variables for two or more independent variables where necessary. Chi-square test of association and Pearson correlation will be used to assess the relationship between cardiometabolic risk factors and PE at baseline and follow-up for both mother and child. A difference will be considered significant at α = 0.05.

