### Study Design and Procedure

This will be a prospective case-control study involving babies born to pre-eclamptic pregnant women and babies born to normotensive mothers recruited at the Nelson Mandela Academic Hospital, Mthatha, Eastern Cape Province of South Africa. Pregnant women who meet the selection criteria will be recruited between weeks 20–26 of gestation and their cardiovascular risk profile assessed at week 30 of gestation. The cardiovascular risk profile of their offspring will be assessed at birth and 6 weeks later.

Recruited pregnant women will be assessed at baseline (week 30 of gestation) for cardiometabolic risk profile including their PE status, anthropometry, blood pressure, oxidative stress, and vascular function. The socio-demographic, obstetric, and medical history will be collected using a structured interviewer administered questionnaire. Their blood pressure (systolic and diastolic blood pressures (BP) and heart rate, and anthropometric measures including weight and height will be measured. A vicorder (SMT Medical GmbH&Co., Wuerzburg, Germany) will be used to measure pulse wave velocity (PWV) to assess arterial stiffness and ankle-branchial index (ABI). The retinal microvasculature via retinal imaging will be assessed for vascular changes using a Optomed Aurora retinal camera (Optomed, [name], Finland). Gestational ultrasound will be performed to determine placental morphometry, architecture and vascularization. Fasting blood will be collected for the assessment of lipid profile, glycaemic, oxidative stress, reno-cardiovascular, and endothelial function markers.

At birth, the gestational age and mode of delivery of the offspring will be noted. The Appearance, Pulse, Grimace, Activity, and Respiration (APGAR) score (1–5 min) will be determined. The weight, height/length and blood pressure of the child will be measured, and PWV measured using a vicorder. Cord blood will be collected for determination of cardiometabolic risk markers including lipid profile, oxidative stress, reno-cardiovascular and endothelial function markers. Six weeks after birth, blood pressure (BP) and anthropometric measurements and PWV assessment will be done in children. Then, blood and urine samples will be collected for the assessment of endothelial function, lipid profile, reno-cardiovascular and oxidative stress markers.

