Despite the strengths of this study, we will also want to acknowledge some limitations of the study. This study will be conducted in Mthatha in the Eastern Cape Province of South Africa, a region highly dominated by African Ancestry population. Other ethnic populations within South Africa will not be considered. However, the ethnicity of the children born of these mothers may not be restricted because of the background of their fathers. The prevalence of PE in South Africa is very low, and therefore, recruitment of patients will be challenging. To curb this challenge, we will work with medical personnel at the recruiting hospital to alert us on eligible patients during antenatal visits. The study intends to follow-up offspring after birth for a period of 6 weeks which may not be sufficient to assess the progression of cardiovascular risk in children. However, this limitation in the short follow-up period was with respect to the available funding for the project. Ultrasound-based flow-mediated dilatation (FMD) measurements of the brachial artery which is known to be the goal standard for the assessment of endothelial function (49, 50) will not be used for this study as this equipment requires participants to be stable during assessment, but such stable state may not be achieved during pregnancy especially when pregnant women are in their 3rd trimester experiencing labour (uterus contractions). As such, endothelial function assessments will be limited to biomarkers of endothelial function. As reported by the developmental origin of health and diseases (DOHaD) certain drugs have been reported to affect the in-uterine environment and/or the foeto-placental endothelium which may predispose offspring to cardiovascular risk factors (51). This study will not be able to control the effects of drugs that can affect the *in-utero* environment and foeto-placental endothelium. To address this concern pregnant women will report all drugs that they had taken during pregnancy and their duration. Our statistician will be able to identify such drugs with long duration that could affect the study outcome and will be considered as confounding variable during statistical analysis.

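### Offspring of non-randomised, unmatched groups are compared by an unadjusted t-test, and the one stated adjustment, for long-duration drugs in pregnancy, does not set aside drugs given because of pre-eclampsia

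*Protocol article*

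**What the plan says.** Study Design and Procedure describes the design: "This will be a prospective case-control study involving babies born to pre-eclamptic pregnant women and babies born to normotensive mothers". No matching is mentioned there or under Selection Criteria.

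The Statistical Analysis section gives the methods:
- An independent-sample t-test "will be used to compare mean differences between groups (pre-eclamptic and normotensive pregnant women and their offspring").
- "Chi-square test of association and Pearson correlation will be used to assess the relationship between cardiometabolic risk factors and PE", at baseline and follow-up, for mother and child.
- MANOVA, which "will be used to compare continuous variables for two or more independent variables where necessary". No covariate, model or trigger is named.

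The Data Collection section lists socio-demographic items (including age), socio-economic status, and "maternal obstetric history, family history, cardiometabolic health history, and cardiovascular risk factors (physical exercise, smoking, alcohol consumption, and feeding habit"). Study Design and Procedure adds maternal weight and height at week 30, and gestational age and mode of delivery at birth.

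The Discussion, in its limitations paragraph, contains the only sentences on confounder adjustment. They say that "pregnant women will report all drugs that they had taken during pregnancy and their duration", and that the statistician will identify "such drugs with long duration that could affect the study outcome and will be considered as confounding variable during statistical analysis".

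**The concern.** The abstract states a causal aim: the cardiovascular effect of in-utero exposure to PE, with a view to advising policy. In a non-randomised comparison an unadjusted difference in means mixes that effect with whatever else separates the mothers.

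The article's own background figures make one imbalance likely. The Introduction puts PE at about 5% of pregnant women but 12% of primigravidae, so first pregnancies should be over-represented among cases.

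The drug rule could add a second problem. A drug started because a woman has PE is a consequence of the exposure and closely tied to it. Entering it as a confounder can take away part of the effect under study and leave little independent information on PE. The written plan would then adjust for something that follows PE while leaving out factors that precede it.

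**Working it through.** The article reports no figure for this point, so there is none to reproduce. The steps below show the size of each problem under stated assumptions.

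**Inputs from the article**
- Neonatal DBP SDs 11.89 and 11.49 mmHg, planning difference 11.94 mmHg, 49 per group (Sample Size Calculation).
- DBP difference of 1.35 mmHg in children and young adults (Discussion).
- PE in 5% of pregnant women and 12% of primigravidae (Introduction).

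Pooled SD = √((11.89² + 11.49²)/2) = 11.69 mmHg. SE of an unadjusted difference with 49 per group = 11.69 × √(2/49) = 2.36 mmHg.

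**1. Is parity imbalance to be expected?** Let f be the share of primigravidae among pregnant women. Their share among women with PE is 0.12f/0.05 = 2.40f, and among women without PE 0.88f/0.95 = 0.926f. The ratio is 2.40/0.926 = 2.6 whatever f is. This assumes that both percentages describe the same population and that cases and controls are sampled without regard to parity.

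**2. Bias from one omitted confounder.** Bias = D × r × SD, where D is the imbalance in SD units and r the within-group correlation with DBP. Both are assumed. The false-positive rate is a normal approximation at two-sided 0.05 with SE 2.36.

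| D | r | Bias (mmHg) | Share of 11.94 | Multiple of 1.35 | False-positive rate |
|---|---|---|---|---|---|
| 0.3 | 0.2 | 0.3 × 0.2 × 11.69 = 0.70 | 6% | 0.5 | 6% |
| 0.5 | 0.3 | 0.5 × 0.3 × 11.69 = 1.75 | 15% | 1.3 | 12% |
| 0.8 | 0.4 | 0.8 × 0.4 × 11.69 = 3.74 | 31% | 2.8 | 35% |

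**3. Cost of adjusting for a drug given because of PE.** With use p in cases, q in controls, equal groups and m = (p + q)/2, the squared correlation of drug use with group is R² = ((p − q)/2)² / (m(1 − m)). The SE of the PE effect is multiplied by 1/√(1 − R²). The use rates are assumed.

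| p | q | R² | SE multiplier |
|---|---|---|---|
| 50% | 5% | 0.25 | 1.16 |
| 50% | 2% | 0.30 | 1.19 |
| 80% | 5% | 0.58 | 1.53 |
| 95% | 2% | 0.87 | 2.73 |
| 95% | 1% | 0.89 | 2.95 |

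The effective size per group is 49 × (1 − R²). At q = 2% it is about 34 (p = 50%), 18 (p = 80%) or 7 (p = 95%). Power for 11.94 mmHg at two-sided 0.05 falls from 99.9% to 99%, 87% or 46%. These figures cover precision only. Any part of the PE effect absorbed by the drug term is a further loss.

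**The case against.** The strongest objection is that a journal article condenses the plan. A covariate list may sit in a fuller document, and nothing here calls the t-test the sole analysis. That disposes of any complaint about missing detail. It does not dispose of what the article positively states: unadjusted methods for the group comparison, and one confounder rule that points at drugs.

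Four further objections stand in part.
- **Exclusions.** Selection Criteria removes chronic hypertension, type 2 and gestational diabetes, renal disease and CVD, which controls some confounding by restriction. It does not deal with parity, age, smoking, alcohol or social status.
- **MANOVA.** A reader might infer that it could not adjust for anything. A factorial MANOVA can take categorical factors such as smoking. As described, though, it is conditional, names no covariate and does not adjust for continuous ones.
- **The drug rule.** A reader might infer that drugs will be picked after outcomes are seen, or that treatments for PE will certainly be entered. The text says neither. It gives no timing, and the choice could be made from drug reports alone. It names no PE treatment, but its scope is all drugs taken in pregnancy and it has no rule for setting PE treatments aside.
- **Size.** A reader might infer that confounding would swamp the result. Against the planned 11.94 mmHg the bias is modest. At its low end it is about half of 1.35 mmHg, a figure that comes from children and young adults and is smaller than the study's own SE of 2.36 mmHg. If half the cases or fewer take a given drug, the loss of precision is small.

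**Conclusion.** The point holds. The comparison the article fixes is unadjusted between groups that are neither randomised nor described as matched, while factors likely to differ are collected and given no role in it. The one adjustment promised could include consequences of PE.

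Under the assumptions above, one omitted confounder shifts DBP by about 0.7–3.7 mmHg, and adjusting for a PE-related drug inflates the SE about 1.2- to 2.9-fold. The imbalance, correlation and drug-use rates are assumptions, not figures from the article. The direction of the parity imbalance does follow from the article's own percentages, if they describe the same population. The consequence is greatest for outcomes with true effects well below the planning difference.

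**What to change.** 1. Make the main comparison of each continuous offspring outcome a linear regression on PE group, with a small prespecified set of factors that precede PE and are already collected: maternal age, parity from the obstetric history, smoking, alcohol and one summary socio-economic measure. Keep the t-test as the unadjusted companion, and do not rely on MANOVA for adjustment.
2. Use BMI from the week-30 weight only in a sensitivity model, because PE may already have affected it. If an earlier weight can be had from records, BMI could join the main set, with a note that some women are recruited already pre-eclamptic.
3. Put gestational age at birth and mode of delivery in a separate secondary model, labelled as possible mediators.
4. Amend the limitations paragraph to say that drugs given for PE are reported descriptively and not entered as confounders. Adjustment limited to drugs taken before PE onset would need start and onset dates, which the article does not describe collecting.

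The cost is analysis wording and roughly five to eight degrees of freedom from about 98 infants. Socio-economic status has four listed components (marital status, profession, income, living standard), so it must be collapsed to one measure to stay in that range. No new measurement is needed for the main model.

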## Discussion

This study aims to investigate the relationship between PE and cardiovascular risk in children born to pre-eclamptic mothers in a rural South African population of African descents. It has been suggested that the foeto-placental vascular endothelial dysfunction may cause epigenetic alteration in the intrauterine environment of the foetus (39). Therefore, the maternal gestational environment may be programmed to have a significant impact on foetal and offspring health later in life (9). In fact, some studies have undertaken to investigate whether children born to pre-eclamptic mothers may predispose them to cardiovascular risk factors. Miller et al. demonstrated as early as 1983 that full-term neonates born to pre-eclamptic mothers have transient hypertension during the first hours of life (40). A meta-analysis study with over 45,000 individuals reported a 1.35 mmHg and 2.39 mmHg higher DBP and SBP in children and young adults born to pre-eclamptic pregnancies (41). The timing of the onset of PE has been reported to be a determinant of hypertension in offspring later on in life as offspring born to mothers with early PE onset were found to have increased central and peripheral SBP (6 mmHg) (42). Also, offspring of pre-eclamptic pregnancies showed a distinct vascular phenotype which could possibly mediate increased risk of hypertension in future (13). More so, impaired flow mediated endothelial responses as well as increased carotid intima-media thickness which suggest endothelial dysfunction was observed in preterm-born young adults exposed to a hypertensive pregnancy (12). A Spanish study on *in-utero* growth restricted children showed that children born to pre-eclamptic parents had higher BP, cardiac remodeling, and evidence of endothelial dysfunction at 6 months of age. Follow-up studies on school age children showed that they had higher SBP and DBP, smaller hearts, increased heart rate and features of cardiac diastolic dysfunction (43). A Norway study of 15,778 participants of which 343 were born to pre-eclamptic mothers showed increased BP, body mass index, wider waist circumference, higher non–HDL-cholesterol and triglycerides suggesting increased risk of CVDs (44). All these studies have shown that children born to pre-eclamptic mothers are prone to obesity, hypertension, diabetes and CVDs in their adult life (45, 46). However, all these findings were established in western populations with little or no reports from children of African origin. To our knowledge there is yet to be such a study in an African population. Conversely, it remains unclear whether the high prevalence of cardiovascular risk factors (obesity, hypertension etc) observed in South African children of African ancestry (47, 48) may have originated from pre-eclamptic mothers. The assessment of cardiovascular risk in pre-eclamptic pregnant women and the follow-up of their offspring after birth for possible cardiovascular risk may address this concern.

The findings from this study will provide information on the cardiovascular risk profile of offspring of pre-eclamptic mothers of African ancestry living on the African continent. It will also provide an opportunity to understand the relationship between the maternal environment and foetus, and how this may influence the risk for CVDs. A knowledge of the risk profile of the offspring of pre-eclamptic mothers may be used to develop plans/programs for CVD prevention in the offspring of women with PE. Also, findings from this study may help to develop policy around maternal and child health to ensure CVD risk prevention in both pregnant women with PE and children born to them. For the purpose of primary prevention of CVDs in children and later in life, it is important to identify predisposing risk factors in pregnant women so that intervention strategies for preventing intrauterine programming as a result of PE may be developed. This may give insight on lifestyle modifications that may be useful for the mother and child both during pregnancy and after birth. To our knowledge, this will be the first longitudinal study to assess the risk factors for CVD *in-utero* and at two time points after birth in a population of pre-eclamptic women of African ancestry. This will be the first study to assess vascular function and its markers in children exposed to the PE environment *in-utero* in an African community and done in children of African ancestry.

Despite the strengths of this study, we will also want to acknowledge some limitations of the study. This study will be conducted in Mthatha in the Eastern Cape Province of South Africa, a region highly dominated by African Ancestry population. Other ethnic populations within South Africa will not be considered. However, the ethnicity of the children born of these mothers may not be restricted because of the background of their fathers. The prevalence of PE in South Africa is very low, and therefore, recruitment of patients will be challenging. To curb this challenge, we will work with medical personnel at the recruiting hospital to alert us on eligible patients during antenatal visits. The study intends to follow-up offspring after birth for a period of 6 weeks which may not be sufficient to assess the progression of cardiovascular risk in children. However, this limitation in the short follow-up period was with respect to the available funding for the project. Ultrasound-based flow-mediated dilatation (FMD) measurements of the brachial artery which is known to be the goal standard for the assessment of endothelial function (49, 50) will not be used for this study as this equipment requires participants to be stable during assessment, but such stable state may not be achieved during pregnancy especially when pregnant women are in their 3rd trimester experiencing labour (uterus contractions). As such, endothelial function assessments will be limited to biomarkers of endothelial function. As reported by the developmental origin of health and diseases (DOHaD) certain drugs have been reported to affect the in-uterine environment and/or the foeto-placental endothelium which may predispose offspring to cardiovascular risk factors (51). This study will not be able to control the effects of drugs that can affect the *in-utero* environment and foeto-placental endothelium. To address this concern pregnant women will report all drugs that they had taken during pregnancy and their duration. Our statistician will be able to identify such drugs with long duration that could affect the study outcome and will be considered as confounding variable during statistical analysis.

In all, this study will seek to address the possible relationship between PE and cardiovascular risk in children born to pre-eclamptic mothers in South Africans of African ancestry. This study will be of importance to the South African population as there is evidence of rising prevalence of cardiovascular risk factors such as obesity, hypertension, diabetes and metabolic syndrome observed in South African children without a clear understanding of the underlining cause. The findings of this study may contribute to the development of policies that can help in the prevention of CVD risk in pre-eclamptic mother and their children. It may also help to develop intervention strategies for the prevention of intrauterine programming resulting from PE in pregnancy.

